### Qualitative assessment of intervention acceptability

A purposive sub-sample of 8–10 participants from the tHEP group and up to 5 from the usual care group will be invited to attend a semi-structured interview following completion of their twelve month follow-up to evaluate participants’ experiences. Participants in the tHEP group will be asked about their experience of the tHEP and the factors that facilitate and impede adherence to it. Participants in the usual care group will be asked whether the advice they received prompted any change in exercise or physical activity behaviour and about their experience of exercise. The interviews will be recorded, transcribed and undergo thematic analysis to explore themes within the data [61].

### Data analysis

#### Efficacy of intervention

For our primary outcome of activity limitation (RODS) we will adjust for baseline score. For all other outcomes, we will adjust for the severity stratification group using ONLS baseline score, but not for the IVIg stratification group as the likely low numbers will lead to an unstable model.

Intention to treat analysis will be our primary model for efficacy analysis. We will conduct a linear regression of change from baseline to the twelve month follow up and add in both intervention arm and baseline score. A secondary analysis will examine changes between baseline and 12 week follow up. Complete case analysis is most often used but not ideal in this study as we have small numbers. If we have some missing data at twelve month follow up we can attempt to extrapolate based on the data from participants with complete datasets if there is less than 25 % missing data.

Per protocol analysis: If we can identify a suitable cut-off from our measure of adherence we can also run a per protocol analysis by removing those participants from the dataset who did not complete enough of the exercise intervention to be able to show an effect. However, due to low numbers we do not wish to put the analysis at risk by excluding too many.

We will also run an exploratory secondary subgroup analysis of the self-efficacy data in order to see whether self-efficacy influences the efficacy of the intervention. A high/low score threshold will be identified for this purpose.

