### Sample size

The sample size is based on an 80 % power calculation to detect a difference between mean change in the overall disability sum score (ODSS) [35] of 1 point using a 2 sided test at the 5 % significance level based on a SD of 1.27 from pilot study data [24]. Fifty-four people (27 per group) will be needed; therefore 70 people will be recruited to allow for a 25 % attrition rate at twelve months. The ODSS is a pre-cursor of the ONLS and was used for sample size calculation as this was the recommended outcome measure of disability in IN at the time of the pilot study.

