### Outcome assessment

#### Primary outcome

*Activity limitation* will be assessed using the recently validated Rasch based Overall Disability Scale (RODS) [48]. This 24-item interval scale for activity limitation has greater responsiveness than previous ordinal measures [49]. Scores for the RODS will be collected at baseline, at the end of the twelve week intervention period and at a twelve month follow up.

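### The missing-data rule for the primary analysis lapses at the attrition the trial plans for, names no method beyond that point, and does not commit to using the 12-week RODS of people lost later

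*Protocol article*

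**What the plan says.** Four statements in the protocol article bear on this point.

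- **Planned loss.** In Sample size, 54 evaluable people (27 per group) are required; "therefore 70 people will be recruited to allow for a" 25% loss by twelve months.
- **Primary model.** In Efficacy of intervention, the primary analysis is by intention to treat: a linear regression of change from baseline to twelve months on arm and baseline score. The 12-week change is a secondary analysis.
- **Missing data.** The same section says "Complete case analysis is most often used but not ideal in this study as we have small numbers". It continues that, for missing twelve-month data, "we can attempt to extrapolate based on the data from participants with complete datasets", provided that under 25% is missing. It states no method for 25% or more.
- **Data collected.** In Primary outcome: "Scores for the RODS will be collected at baseline, at the end of the twelve week intervention period and at a twelve month follow up".

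**The concern.** The rule governs the primary result, and its cut-off equals the trial's own attrition allowance. Whether the primary estimate uses filled-in values could therefore turn on one participant, and would be settled by data seen after randomisation. The rule also withdraws its remedy when the numbers are smallest, which is the reason the plan gives for not relying on complete cases.

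A second weakness is the information used. Someone seen at 12 weeks but lost by twelve months has an observed post-intervention score on the primary measure. The stated model does not include it, and the plan does not commit to using it when values are filled in. Participants know their allocation (Design section), so dropout related to early response could differ between arms. The 12-week score is the best available protection against that.

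**Working it through.** **1. The plan's own sample size.** The inputs, all from Sample size, are 80% power, a one-point between-group difference in mean ODSS change, a two-sided 5% level, and a pilot SD of 1.27. With standardised effect 1/1.27 and a two-sample t-test (noncentral t), power is 79.5% at 26 per arm and 81.0% at 27, so 27 per group is reproduced. For attrition, 54/0.75 = 72 and 54 × 1.25 = 67.5 (68 after rounding up); the stated 70 lies within two people of both. The sample size is not in dispute.

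**2. Where the rule switches.**
- 70 × 0.25 = 17.5.
- 17/70 = 24.3%: extrapolation permitted.
- 18/70 = 25.7%: not permitted.

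The chance that the rule lapses is P(X ≥ 18) for X ~ Binomial(70, d):

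| True loss rate d | P(18 or more missing) |
|---|---|
| 20% | 15% |
| 22.9% (16/70) | 33% |
| 25% (planned) | 49% |
| 30% | 82% |

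**3. Standard error, if extrapolation means single regression imputation.** Suppose missing values are predicted from completers by arm and baseline, and then analysed as observed. Imputed points lie on the fitted line, so the estimate and the residual sum of squares do not change. The residual degrees of freedom rise from 53 − 3 = 50 to 70 − 3 = 67, and the apparent sample size rises from 53 to 70. The reported standard error therefore shrinks by about √((50/67) × (53/70)) = 0.752.

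The nominal critical value of 1.996 (67 df) then acts as 1.996 × 0.752 = 1.50 on 50 df, a two-sided error of about 14%. Simulation of the primary model agrees (35 per arm, 17 missing at random, no true effect; SD 1.27 as scale and correlation −0.3 between baseline and change, both assumed for RODS):

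| Handling of missing values | Reported SE | True SE | Type I error |
|---|---|---|---|
| Complete cases | 0.335 | 0.338 | 4.9% |
| Single imputation, by arm | 0.250 | 0.338 | 14.7% |
| One random draw, by arm | 0.288 | 0.367 | 12.0% |
| Single imputation, arms pooled | 0.251 | 0.253 | 4.7% |

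The pooled version holds its error rate but shrinks a true effect of 1.0 to 0.75. With 10 missing, the by-arm formula gives √((57/67) × (60/70)) = 0.854 and an error of about 9%.

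**4. Bias, if dropout follows early response.** Assumptions: no true effect; correlation 0.6 between baseline and follow-up and 0.7 between 12 weeks and 12 months; 9 lost from exercise in relation to poor 12-week change; 8 lost from control at random. With a dropout weight of 1 log-odds per SD, complete-case analysis and arm-and-baseline fill-in (which give the same estimate) are biased by 0.10 SD towards exercise. With weights of 0.5 and 1.5 the bias is 0.05 and 0.13 SD. Including the 12-week score brings it to about 0.00, as it must when dropout depends only on that score and arm.

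**5. Direction.** Here dropout depends on the 12-month change itself (weight 1 per SD, scale of step 3, 17 missing):
- poor responders leave exercise only, no true effect: +0.28 (0.28/1.27 = 0.22 SD);
- they leave both arms alike, no true effect: 0.00;
- they leave control only, no true effect: −0.25;
- they leave both arms alike, true effect 1.0: estimate 0.84, which is against exercise.

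**The case against.** A reader might infer that the plan inflates false positives, favours exercise and discards the 12-week data. The document supports none of these as a flat statement.

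- **Inflated error.** The wording is permissive and names no method. Inflation follows only from single imputation within arm with filled values treated as observed. Proper multiple imputation avoids it, and the imputation type is a detail that may sit in an analysis plan not shown here.
- **Favouring exercise.** This needs poor responders to leave the exercise arm more than control. Nothing in the document predicts that, and other patterns give no bias under the null, dilution of a true effect, or the opposite sign.
- **Unused 12-week scores.** The text does not say so. Fitting a model to people with complete data and predicting from a dropout's own baseline and 12-week scores is a natural reading.
- **The threshold.** Keeping 54 of 70 allows 16 losses (22.9%), so the rule applies whenever the evaluable target is met, and 25% is an allowance, not a forecast. The complete-case fallback is also inferred; if it were used, its error rate would be correct under random loss.

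The first three objections stand and make those consequences conditional. The last softens the threshold point but does not remove it. At the planned 25%, the expected number evaluable is 70 × 0.75 = 52.5, below 54, so the loss the trial provides for is where the rule lapses. The protocol itself fixes that cut-off and the completer basis; a later plan would have to overturn them, not just fill in detail.

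**Conclusion.** The concern holds in a limited form. Without any further assumption, the missing-data rule for the primary analysis stops at the attrition the trial allows for, has a near-even chance (49%) of lapsing if that attrition occurs, and gives no method beyond it. Nor does the plan commit to using the 12-week RODS of people lost later.

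The possible damage is conditional: type I error of about 14-15% with 17 missing if single within-arm imputation were used, and bias of roughly 0.1 SD towards exercise if poor 12-week responders left that arm more. The bias figure rests on assumed correlations and an assumed strength of dropout, and its sign reverses if control loses more of them.

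This is worth correcting before unblinding, because a better method is available from data already planned. It is not a defect that by itself invalidates the primary analysis.

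**What to change.** Delete the 25% condition and the extrapolation from completers. Replace them with one of two approaches, used whatever the missing rate:

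- a linear mixed model for repeated measures on RODS at 12 weeks and 12 months, including all randomised participants with any follow-up score, with arm-by-visit and baseline-by-visit terms and unstructured covariance. The 12-month contrast is primary, and the 12-week contrast serves the secondary analysis already planned; or
- the stated baseline-adjusted regression with proper multiple imputation from a model that includes arm, baseline and 12-week RODS.

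The two should give similar answers under missing at random, so keeping the stated model is acceptable. Add a delta-shifted multiple imputation as sensitivity analysis. It tests departures from missing at random and covers people lost before 12 weeks, whom the repeated-measures model leaves out.

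The cost is analysis wording and a little more analysis work. No new data are needed.

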*Self-efficacy;* an individuals confidence in their ability to exercise, will be measured using the self-efficacy for exercise (SEE) scale [57]. The scale examines 9 potential barriers to exercise, such as feeling tired or depressed; participants are asked to rate each item on an eleven point Likert scale spanning the extent to which they feel confident that they could exercise in the presence of a particular barrier (0 = Not confident, 10 = Very confident). The authors report good internal consistency (alpha 0.92) and good predictive validity for the scale [57].

*Adherence* to the tailored home exercise programme in the study will be evaluated using a) the Exercise Adherence Rating Scale (EARS) and b) self-report diary entries.The EARS has been developed based on the Medication Adherence Rating Scale [58] and evaluates barriers to adherence for prescribed exercise by asking participants to rate, on a five-point Likert scale, the extent to which they agree with sixteen statements about their exercise adherence (for example, “I forget to do my exercises”, “I’m not sure how to do my exercises”). The EARS will only be completed by participants randomised to the tHEP intervention.Self-report exercise diaries record exercise type, completion and factors affecting exercise. The number of repetitions of strengthening exercise and duration of aerobic exercise will be used to calculate overall adherence as a proportion of the exercise prescribed.

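### The optional per-protocol analysis can exclude people from the exercise arm only, so it is no longer a randomised comparison and is probably, though not demonstrably, tilted towards exercise

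*Protocol article*

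**What the plan says.** Under Data analysis, Efficacy of intervention, ITT is the primary model: a linear regression of change to twelve months on arm and baseline score. A per-protocol analysis is then offered conditionally: "If we can identify a suitable cut-off from our measure of adherence". It would proceed by "removing those participants from the dataset who did not complete enough of the exercise intervention to be able to show an effect". The authors add that numbers are low and that they would not want to exclude too many.

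Under Secondary outcome measures, adherence refers to the home exercise programme and has two sources. For the first, the Exercise Adherence Rating Scale, the article says: "The EARS will only be completed by participants randomised to the tHEP intervention". The second is the exercise diary, from which adherence is the share of prescribed exercise that was done.

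Under Interventions, Control group, controls receive a letter, a physical activity factsheet and a readiness questionnaire by post, and do not see the study physiotherapist. They have no prescribed programme.

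**The concern.** Read together, these sections mean that only tHEP participants can be excluded. The analysis compares a subset of one randomised arm, selected on behaviour after randomisation, with the whole of the other. The controls who would have adhered poorly had they been offered the programme all stay in.

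The article itself suggests why this may matter. The Background links fatigue with greater activity limitation, and the self-efficacy scale described under Secondary outcome measures lists tiredness and depression as barriers to exercise. Low adherers may therefore be people who would have done worse anyway, and removing them from one arm would flatter tHEP.

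In a trial of 70, a favourable per-protocol figure beside an inconclusive ITT result could easily be read as showing that the programme works for those who do it. The analysis does not estimate that quantity.

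**Working it through.** **1. The design figure, for scale.** The inputs come from Sample size: power of 80%, a two-sided 5% level, and a gap of 1 point between arms in mean ODSS change. For the spread, the calculation is "based on a SD of 1.27 from pilot study data".

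- Normal approximation: n per arm = 2 × 1.27² × (1.960 + 0.842)² / 1² = 25.3, so 26.
- Two-sample t-test (noncentral t): power is 79.5% at 26 per arm and 81.0% at 27. This reproduces the plan: "Fifty-four people (27 per group) will be needed".
- Standardised design effect: 1 / 1.27 = 0.79 SD. This is on the ODSS, whereas the primary outcome is the RODS, so it serves only as a yardstick.

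**2. Who can be excluded.**

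| | tHEP arm | Control arm |
|---|---|---|
| Prescribed programme | yes | no |
| Adherence scale completed | yes | no |
| Diary share of prescription | defined | undefined |
| Can fail the criterion | yes | no |

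This holds at every cut-off value.

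**3. Bias when there is no true effect.** Let f be the share of the tHEP arm excluded and g the gap in mean outcome between adherers and non-adherers, in SD, after baseline adjustment. With no effect, the control mean equals the full tHEP mean, (1 − f) × m_A + f × m_N. The per-protocol difference is therefore

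m_A − [(1 − f) × m_A + f × m_N] = f × (m_A − m_N) = f × g.

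The article gives neither f nor g. Over an assumed range:

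| f | g = 0.3 | g = 0.5 | g = 0.8 |
|---|---|---|---|
| 20% | 0.06 | 0.10 | 0.16 |
| 30% | 0.09 | 0.15 | 0.24 |
| 40% | 0.12 | 0.20 | 0.32 |

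If g = 0 the bias is zero; if g is negative it runs against exercise.

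**4. Cross-check with a different parameterisation.** Let rho be the correlation between adherence and outcome (assumed). Excluding the lowest share f gives a bias of rho × φ(z_f) / (1 − f), where z_f is the normal quantile at f. False-positive rates come from 40,000 simulated null trials per setting: 27 per arm, the lowest adherers removed from the tHEP arm only, two-sided t-test at 5%.

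| f | Bias, rho 0.3 | False positives | Bias, rho 0.5 | False positives |
|---|---|---|---|---|
| 20% | 0.10 | 6.3% | 0.17 | 8.7% |
| 30% | 0.15 | 7.7% | 0.25 | 12.9% |
| 40% | 0.19 | 9.1% | 0.32 | 17.3% |

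At rho = 0 there was no bias and the rate was about 5%. At rho = −0.3 the bias was the same size as at +0.3, in the opposite direction.

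**5. Loss of numbers.** For 1 point at SD 1.27, power falls from 81.0% (27 v 27) to 76.6% (22 v 27), 73.0% (19 v 27) and 68.3% (16 v 27) at 20, 30 and 40% excluded. This takes the exclusions from the 27 with outcome data. Where non-adherers are also the dropouts, the extra loss is smaller.

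**The case against.** Five points can be made for the plan.

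- **ITT is primary and the per-protocol analysis is conditional and additional.** This stands. Nothing here alters the primary conclusion.
- **The unseen analysis plan may fix the threshold.** This stands for its value and date, and their absence from the article is not the fault. The rule itself, removing low adherers from one arm, is stated in the article and is unsound at any threshold.
- **The criterion is a minimum dose.** A reader might infer from the wording that the cut-off will be picked because it yields an effect. The text does not say so. It more naturally describes people whose exercise was too little to work, and the wish not to exclude many is a caution. What can be said is that the article fixes neither measure nor cut-off and does not rule out choosing after outcomes are seen.
- **The direction is not shown.** A reader might also infer that the analysis necessarily favours exercise. The article reports no relation between adherence and outcome, and its efficacy model adjusts for baseline score, which should remove much of any difference in initial disability. Only the residual gap counts. A tilt towards exercise is plausible, not established.
- **The alternative estimator has weaknesses of its own.** This stands, and they are listed with the fix. They do not rescue the exclusion, which fails even when there is no effect to estimate.

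**Conclusion.** The per-protocol comparison, as the article states it, is one-sided and not protected by randomisation. That follows from the text alone, without assumptions. Bias towards exercise is probable if adherers have a better prognosis beyond baseline RODS. With 20 to 40% excluded and a residual gap of 0.3 to 0.8 SD it would be 0.06 to 0.32 SD, against a design effect of 0.79 SD on the ODSS. Both inputs are assumed, and the bias is nil if adherence is unrelated to outcome. The analysis should be replaced, but the point concerns a supplementary result, not the trial's main answer.

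**What to change.** Replace the exclusion with a complier average causal effect analysis: two-stage least squares, randomised arm as instrument, baseline score as covariate, and everyone with outcome data kept in the assigned arm. Take as exposure the diary share of prescribed exercise, with controls set to 0. Preferably use it as a continuous measure; otherwise fix the cut-off before outcome data are seen. Label the result supportive to ITT.

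Controls have no access to the programme, so non-adherence is one-sided and the design suits the method. Without covariates, the estimate is the ITT difference divided by the difference in mean exposure, so with no effect in any participant it centres on zero however adherence relates to prognosis.

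No new data are needed, only a change of analysis wording. The downsides to state are:

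- **Wider interval.** With a binary cut-off and share f below it, the ITT interval is stretched by about 1 / (1 − f): 1 / 0.8 = 1.25 times at 20%, and 1 / 0.6 = 1.67 times at 40%.
- **Exclusion restriction.** It is doubtful for a binary cut-off, because participants below it still have physiotherapist contact and do some exercise. Any benefit to them would inflate the estimate.
- **Linear dose-response.** The continuous version assumes it.
- **Diaries.** They may be missing most often among non-adherers, so the handling of missing diaries must be specified.
- **Meaning of zero.** Setting controls to 0 codes exposure to the programme, not exercise done; controls also receive activity guidance.

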#### Secondary research questions

What is the cost-effectiveness and cost utility of a tHEP compared with advice about exercise and usual care for people with IN?

Are the health beliefs of people with IN associated with their response to a tHEP versus advice about exercise and usual care?

What are participants’ experiences of a tHEP and which factors influence uptake of and adherence to the programme?

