#### Secondary outcome measures

All of the following secondary outcome measures will be assessed at baseline, twelve weeks and twelve months:

*Activity limitation* will also be assessed as a secondary outcome using the Overall Neuropathy Limitations Scale (ONLS) [34]. This is a 12 item ordinal scale of activity limitation developed from the ODSS, which was used to calculate sample size for the present study [35].

*Fatigue* will be assessed using the Rasch-modified Fatigue Severity Scale (RFSS) [50]. This seven-item scale is a Rasch-built modified version of the Fatigue Severity Scale, and was developed specifically to address fatigue in individuals with immune-mediated neuropathy. The authors report good psychometric properties for the scale.

*Psychological wellbeing* will be assessed using the Hospital Anxiety and Depression Scale (HADS) [51]. The scale consists of separate anxiety and depression subscales of seven items each and has been found to correlate well with other measures of depression and anxiety.

*Functional health and well being* will be assessed using the Medical Outcomes Short Form 12 (SF-12). The norms-based scoring system allows direct data comparisons to be made between the SF-12 and other generic health surveys [52, 53].

*Levels of physical activity* will be assessed using the 7-question International Physical Activity Questionnaire (IPAQ-short). The questions ask participants to report the frequency and duration of moderate activity, vigorous activity and walking, and to rate the proportion of time they spent sedentary in the previous week. The scale has shown acceptable measurement properties, similar to other self-report assessments [54].

*Health beliefs* will be assessed using the Brief Illness Perceptions Questionnaire (Brief-IPQ) [55] developed from the revised Illness Perceptions Questionnaire (IPQ-R) [56]. Nine questions address participants beliefs with regard to various features such as perceived severity of consequences, perceived chronicity of an illness or condition, and perceived control over the course or treatment of a given condition. Participants respond on an eleven point Likert scale (for example, 0 = no symptoms at all, 10 = many severe symptoms).

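### The exploratory self-efficacy analysis splits a continuous score at a threshold not yet set, and the listed question on health beliefs has no matching analysis in the article

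*Protocol article*

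**What the plan says.** Under Data analysis, Efficacy of intervention, the article adds to the primary regression a subgroup analysis of the self-efficacy data, labelled exploratory and secondary. Its aim is to see whether self-efficacy alters how well the intervention works. The coding is stated: "A high/low score threshold will be identified for this purpose". No value, source or timing for the threshold is given. Secondary outcome measures defines self-efficacy by the SEE scale, nine barriers each rated 0 to 10, collected at baseline, twelve weeks and twelve months.

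Secondary research questions lists a different moderator: "Are the health beliefs of people with IN associated with their response to a tHEP versus advice about exercise and usual care". Health beliefs have their own instrument; they "will be assessed using the Brief Illness Perceptions Questionnaire (Brief-IPQ"). The analysis sections then cover efficacy, per-protocol and self-efficacy subgroup analyses, costs, and interviews. None relates the Brief-IPQ to treatment response.

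**The concern.** There are two separate problems.

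First, splitting the score is a stated choice, not a detail left open. It treats everyone on one side of the cut as alike and discards the ordering within each half. A trial of this size has little information on effect modification to spare. With the cut-point also unset, a reader of the results could not tell from this article whether it was fixed beforehand or chosen because it gave a striking contrast.

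Second, the article asks whether health beliefs are associated with response, which is a question of effect modification, and then describes a moderator analysis of another construct. A declared question would be left without a described method, and an undeclared one would be answered in its place.

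**Working it through.** **The plan's own sample size.** Inputs, all from Sample size: a target of 1 ODSS point between arms, power of 80 %, two-sided alpha of 0.05, and an SD of 1.27 from the pilot. By the normal approximation, n per group = 2 × (1.96 + 0.8416)² × 1.27² / 1² = 25.3, rounded up to 26. With the t distribution, power is 0.795 at 26 and 0.810 at 27 per group. This reproduces the stated figure: "Fifty-four people (27 per group) will be needed". The sample size is not at issue. N = 54 is used below as the evaluable number, and the ODSS SD is used because the article gives none for the RODS.

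**Precision of a comparison between halves.** With equal arms and a median split:
- SE of the main effect = 2 × 1.27 / √54 = 0.35 points.
- SE of the difference in effect between halves = 4 × 1.27 / √54 = 0.69 points.
- Power for a 1-point difference in effect between halves = Φ(1/0.69 − 1.96), about 30 %.
- Difference detectable with 80 % power = 2.80 × 0.69, about 1.94 points, nearly twice the trial's target effect.

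**Information kept by a split.** For a normal moderator cut so that a fraction q lies on one side, at standard normal quantile c, the efficiency relative to the continuous score is φ(c)² / [q(1 − q)].

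| Split | Information kept |
|---|---|
| 50/50 | 2/π = 64 % |
| 33/67 | 59 % |
| 25/75 | 54 % |
| 20/80 | 49 % |

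**Power at N = 54.** Simulated least-squares interaction tests, 27 per arm, normal moderator, linear interaction, two-sided 5 %. The slope is the change in treatment effect, in outcome SDs, per SD of the moderator.

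| Slope | In ODSS points (× 1.27) | Continuous | Median split |
|---|---|---|---|
| 0.8 | 1.02 | 78 % | 58 % |
| 0.5 | 0.64 | 40 % | 28 % |
| 0.3 | 0.38 | 18 % | 14 % |

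At slope 0.5 the two halves differ by 0.5 × 2√(2/π) × 1.27 = 1.01 points, so the middle row is close to the 1-point case above. In repeat runs the split figure at slope 0.8 varied between 52 % and 58 %, while the continuous figure stayed at 77 to 79 %.

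**Type I error at N = 54.** With no true interaction, the continuous term rejects in about 5 % of runs and a fixed median split in 5.3 %. Taking the smallest p-value over seven cut-points, from the 20th to the 80th percentile, rejects in about 20 %. With thirteen cut-points over the same range it is about 24 %.

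**Question against analysis.**
- Question posed: health beliefs and response to the programme versus control.
- Measure of health beliefs: Brief-IPQ.
- Moderator analysed: self-efficacy, measured by the SEE.
- Self-efficacy among the secondary research questions: no.
- Where the Brief-IPQ enters the efficacy section: only through the general adjustment rule for other outcomes. That compares beliefs between arms and cannot show whether beliefs alter response.

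**The case against.** The strongest reply is that this is an exploratory analysis in a condensed article and the analysis plan is not shown. Much of that stands.

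- A reader might infer that the threshold will be data-driven. The article does not say so. A published value, a blinded median or a value fixed in the analysis plan would all fit its wording. The 20 % rate belongs to a search the article does not describe, so it measures the exposure and does not predict what will happen.
- A reader might also infer that follow-up SEE scores, which the programme could change, will define the subgroups. The article does not say this either. Baseline is the more natural reading, and naming it would settle the matter.
- The analysis is already labelled exploratory and secondary.
- The gain from the continuous score looks large only when the interaction is very large. A slope of 0.8 SD is about the whole target effect (1/1.27 = 0.79 SD) for each SD of self-efficacy. At smaller slopes both methods are underpowered.
- The article mentions a subgroup analysis, not an interaction test. The test is assumed in the calculations above.
- An unseen analysis plan may contain a Brief-IPQ model, and the data for one will be collected.

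Two things remain. The split itself is stated, and its loss of information does not depend on how the threshold is chosen. The mismatch is also internal to the article: it did describe a moderator analysis, and it named a construct other than the one its own question asks about. Self-efficacy cannot stand in for health beliefs, because the article measures the two with separate instruments.

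**Conclusion.** The point holds in this limited form. The planned high/low split is an inefficient choice: at a median cut it keeps about 64 % of the moderator information and costs roughly 20, 12 and 4 percentage points of power at slopes of 0.8, 0.5 and 0.3 SD per SD. Because the threshold is not prespecified in the article, it is open to data-driven choice. Type I error would stay near 5 % with a fixed median and reach about 20 % only if the best of seven cuts were selected. The health-beliefs question has no corresponding analysis in this article, while the moderator that is analysed answers no listed question.

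The figures assume 54 evaluable participants, a normally distributed moderator, a linear interaction and a formal interaction test. It would go too far to conclude that the question cannot be answered, since the Brief-IPQ is collected at baseline, or that the trial's main result is at risk. The primary RODS analysis is untouched.

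**What to change.** In Efficacy of intervention, replace the high/low split with an interaction between arm and continuous baseline SEE score, added to the primary regression model. Fit the same model with one baseline Brief-IPQ summary or named item, chosen before outcome data are examined, so that the analysis matches the secondary research question. Report both interactions with 95 % confidence intervals and keep the exploratory label. If a cut is retained for presentation, fix its value and source before unblinding.

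The change is to wording only and needs no new data. Its cost is the assumption that the interaction is linear.
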